#### Interrupted time series analysis

The ITS analysis will examine three periods: 1) Pre-SCRT baseline (November 2019 to November 2020), 2) SCRT partial implementation (December 2020 to July 2021), and 3) SCRT full implementation (August 2021 to August 2022). Each of the outcome measures will be computed as a monthly proportion, with the numerator equaling the number of individuals meeting criteria for each outcome and the denominator equaling the total target population in a given month. Using month-long time intervals would yield between 8 and 12 data points per time period, though the final interval length may change depending on the trade-offs between length of observation and statistical power.

Generalized estimating equations (GEE) will be used, with robust standard errors to account for within-person correlation [27], to analyze the trends in outcomes pre-implementation, during partial implementation, and after the implementation of SCRT. Models will include a variable for time (month) after the beginning of our observation period, a variable for time each time period subsequent to baseline, and the interaction between these variables to assess change in the trajectory of each outcome. Models will be adjusted by the covariates described above and interaction terms constructed to understand the relative effects of covariates and the ITS variables.

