This analysis will use several design and analysis strategies to account for potential threats to internal validity. First, the study design using two nonequivalent groups with staggered implementation (crisis episodes with zip codes corresponding to neighborhoods that did or did not have the SCRT active during the partial implementation phase prior to citywide expansion) will allow for a between-site comparison of the pilot catchment area relative to the non-pilot areas (Fig 1). Additional sub-analyses will examine within-site differences for the pilot neighborhoods across the three time periods, and, separately, within-site differences for the non-pilot neighborhoods. Second, a non-equivalent non-treatment control group (non-homeless adults accessing crisis services) will be compared to the target population (homeless adults accessing crisis services) using a difference of differences approach to account for secular variations in mental health and substance use service utilization. Third, a series of non-equivalent dependent outcome variables that are not expected to be impacted by the implementation of the SCRT (e.g., non-crisis initiation of outpatient mental health services) will be evaluated across the same time periods with a similar goal of accounting for secular variations in mental health service utilization. Additional issues such as autocorrelation of repeated measures on individuals will be corrected for in the final analyses.

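### The main interrupted time series model takes its standard errors from within-person correlation only, so shocks shared by everyone in a month are left out and the level and slope tests are too liberal by an amount the document does not let us fix

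*Protocol article*

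**What the plan says.** All references are to the Protocol article.

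- *Interrupted time series analysis*, on variance: "Generalized estimating equations (GEE) will be used, with robust standard errors to account for within-person correlation".
- Same section, closing the list of validity safeguards: "Additional issues such as autocorrelation of repeated measures on individuals will be corrected for in the final analyses". The dependence named is again within individuals.
- Same section, on the mean model: "Models will include a variable for time (month) after the beginning of our observation period", together with terms for each later period and their interactions with time.
- Same section, on periods: baseline runs from November 2019 to November 2020, partial implementation from December 2020 to July 2021, and full implementation from August 2021 to August 2022. The text adds: "Using month-long time intervals would yield between 8 and 12 data points per time period".
- Same section, on data: each outcome is a monthly proportion, with "the denominator equaling the total target population in a given month". No monthly count, outcome rate or month-to-month variance is given.
- The same section also plans three supporting comparisons: pilot against non-pilot zip codes, a difference of differences with housed adults, and outcomes that the programme should not affect. *Study population* places the housed comparison among the sensitivity analyses.

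**The concern.** Everyone observed in a given month has the same value of month, period and their interaction. A sandwich estimator clustered on person allows for one person's outcomes being alike across months. It assumes that two different people in the same month are independent given the model. Anything that moves the whole month up or down is therefore left out of the variance of exactly the coefficients that carry the programme effect. A linear trend within each period removes drift, but not departures from it.

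The document itself gives reasons to expect such shocks. *Limitations* concedes that COVID effects on data collection and service use cannot be fully accounted for. *Data sources and matching procedures* records a change of the jail record system in October 2021, inside the full-implementation period.

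At stake are the confidence intervals and tests for all four outcomes, and for the equity strata that reuse the model: ordinary monthly fluctuation could be read as a programme effect. The error grows with monthly numbers, because person-clustered standard errors shrink as more people are observed while the variance of a shared shock does not.

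**Working it through.** **1. Count of months.** The stated dates give 13, 8 and 13 months, 34 in all. The plan's lower figure of 8 points per period is reproduced. Its upper figure of 12 is not; the dates give 13. That is a small separate slip with no bearing on this point. Three segments with a level and a slope each use 6 parameters, leaving 34 − 6 = 28 degrees of freedom.

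**2. Assumed inputs (none is in the document).** People per month n = 300 to 1,000; outcome rate p = 0.3 to 0.4; two-sided 5% level; month shock on the logit scale with SD τ = 0.05 to 0.15; lag-1 correlation 0 or 0.4. In percentage points the shock SD is about τ·p(1−p): 1.1 to 1.2 points at τ = 0.05 and 3.2 to 3.6 points at τ = 0.15.

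**3. Formula.** Taking person-level variation as binomial, the modelled variance of a monthly logit is 1/[n·p(1−p)], and the true variance adds τ². For independent shocks the ratio of true to modelled variance of every level and slope term is

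R = 1 + n·p(1−p)·τ², and actual size = 2Φ(−1.96/√R).

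Worked case, n = 1,000, p = 0.4, τ = 0.05: R = 1 + 240 × 0.0025 = 1.60, and size = 2Φ(−1.55) = 12.1%. With correlated shocks, τ² is multiplied by an AR(1) correlation matrix over the 34 months and the variance is recomputed term by term.

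| n | p | τ | R | size, independent | size, correlation 0.4 |
|---|---|---|---|---|---|
| any | any | 0 | 1.00 | 5.0% | – |
| 300 | 0.3 | 0.05 | 1.16 | 6.8% | 7.8–8.5% |
| 1,000 | 0.4 | 0.05 | 1.60 | 12.1% | 15.5–17.8% |
| 300 | 0.3 | 0.15 | 2.42 | 20.7% | 26.8–30.5% |
| 1,000 | 0.4 | 0.15 | 6.40 | 43.8% | 51.6–55.6% |

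Simulation over the same ranges gave about 6–18% at τ = 0.05 and 20–54% at τ = 0.15, in line with the formula. In a smaller setting (n = 200, p = 0.1, τ = 0.05), R = 1 + 18 × 0.0025 = 1.045 and size is only 5.5%.

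**4. Check with actual person clustering.** A simulation with a person random intercept (SD 1), each person present in about one month in four and person-clustered errors (600 replicates, p = 0.3) gave these sizes:

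- no shocks, n = 300: 3.8–5.8%
- independent shocks, SD 0.1: 8–11% at n = 300 and 18–23% at n = 1,000
- SD 0.2 with correlation 0.4, n = 1,000: 54–60%

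The second result at n = 1,000 lies below the formula's 26.6%, because the simulated shock acts on the person-specific scale and is diluted on the population scale. The direction is the same.

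**5. Why serial correlation is plausible.** Under *Index crisis episode*, the 30-day window follows the episode and often runs into the next month. If a share w of the window falls in the index month and calendar-month shocks are independent, adjacent monthly outcomes have shock correlation w(1−w)/[w² + (1−w)²]: 0.5 at w = 1/2, 0.4 at w = 2/3, 0.3 at w = 3/4.

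**6. Alternatives, simulated on the 34 monthly points.**

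| method | independent shocks | correlation 0.4 |
|---|---|---|
| Ordinary regression, t with 28 df | 3–6% | 9–17% |
| REML AR(1), t with 28 df | within 5–9% | about 7–9% |
| AR(1) GLS without REML | 9–12% | 12–15% |
| Newey-West, lag 3 | 16–24% | 21–31% |
| Month-robust errors (proxy for two-way clustering) | – | 12–19% |

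The last three rows come from one setting (p = 0.4; n = 600 and SD 0.08 for Newey-West). Across a wider set of scenarios Newey-West gave 14–34%.

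**The case against.** Four arguments count on the other side.

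*The inputs are all assumed.* This stands. A reader might infer that the tests are far too liberal, or that the data carry only 34 observations' worth of information. The documents support neither. With small shocks and 200 people a month, size is about 5.5%; months become the effective unit only when month variance dominates. The calculations also omit covariates, and the planned adjustment for diagnosis, insurance and prior service use could absorb some monthly fluctuation in case mix. Nor should the chance that any one of the four level and slope terms is significant be used as the measure: it was 16% in simulation with no month shocks, which is multiplicity and not a standard-error fault.

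*The plan does address secular variation.* This stands in part. A reader might infer that shared shocks are ignored altogether. They are not: the three supporting comparisons absorb them in part, and in the pilot comparison exposure varies by zip code within a month. But these are supporting analyses, *Limitations* says location data may be too incomplete for location-specific work, and none changes the standard errors of the main model.

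*The list of issues is open-ended, and an unseen analysis plan may add a correction.* It may. But the protocol does not leave the variance method blank. It names one, and both dependence structures it mentions are at person level.

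*Some obvious remedies fail.* This stands, and it shapes the fix. Newey-West errors do badly on 34 points, and two-way clustering does not cover different people in adjacent months.

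**Conclusion.** The point holds for the main single-series model. As specified, its standard errors omit shocks shared within a month and their serial correlation, while every term of interest varies only by month. Whenever month-level variance is not zero, the level and slope tests exceed their nominal size and the intervals are too narrow.

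The direction is certain; the size is conditional. It runs from nominal with no month shocks, through about 6–18% at a logit SD of 0.05, to about 20–54% at 0.15, under the assumed monthly numbers, outcome rates, correlations and 5% level. The finding does not extend to the whole plan, and the document does not establish how severe the inflation will be in these data. It deserves correction before analysis, because all four outcomes and the equity strata rest on this model and a better-behaved alternative is cheap.

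**What to change.** Keep the person-level GEE for covariate-adjusted estimates. State that inference for the level and slope terms will rest on the 34 adjusted monthly proportions, analysed by segmented regression with AR(1) errors fitted by REML and a t reference on about 28 degrees of freedom. If the fallback in *Limitations* is used (baseline and full implementation only), there are 13 + 13 = 26 months and 4 parameters, so about 22 degrees of freedom, and the correlation structure must respect the eight-month gap.

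Do not substitute Newey-West errors, or two-way clustering by person and month on its own.

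The cost is a short addition to the text and a second modelling step. Intervals will be wider. Some over-rejection remains, about 7–9% at a lag-1 correlation of 0.4, and the report should say so. It should also give the monthly denominators and the estimated residual month variance and autocorrelation, so that readers can judge how much the correction mattered.

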### Program

The Behavioral Health Services division of the San Francisco Department of Public Health (SFDPH) has an extensive infrastructure for mental health and substance use disorder services, yet one important gap has remained: real-time response for people in behavioral health crisis in the streets. In 2019, San Francisco’s 9-1-1 call data indicates that approximately 50,000 behavioral health related calls were received, most of which were responded to by a law enforcement unit. Because most calls were not related to criminal events, and instead to mental health and social needs experienced by PEH, San Francisco behavioral health and governmental leaders worked with community stakeholders to create the SCRT to respond as an alternative able to be more responsive to behavioral health crises that happen on the street [16].

The SCRT was designed based on previous co-responder models [17, 18]. To meet the goal of diverting calls that would typically go to the San Francisco Police Department, this trauma-informed specialty behavioral health team is dispatched solely by 9-1-1 operators. The SCRT utilizes a co-responder model comprised of a behavioral health clinician, a paramedic from the San Francisco Fire Department and a peer specialist. Each team member plays a role in providing care including immediate stabilization of urgent medical need (paramedic), de-escalation of the crisis (behavioral health clinician) and person-centered peer support (peer specialist). The team triages clients to the appropriate level of care, be it through resolution of the crisis in the field, linkage to outpatient mental health and substance use services, or transport to an acute treatment setting. The SCRT was first piloted in San Francisco’s highest demand neighborhoods in December 2020 and then was incrementally expanded to be citywide by June 2021 (Fig 1).

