**Fig 1 pone.0295178.g001:**
[figure not shown]
Rollout of the street crisis response team across San Francisco by region, hours of operation, and launch date of each phase of expansion. Landsat-7 image courtesy of the U.S. Geological Survey.

The SCRT also includes follow-up services provided by the Office of Coordinated Care (OCC), which is charged with offering support after the SCRT encounter with the goal of linking clients to outpatient mental health and housing services, thus reducing reutilization of acute services.

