#### Study population

The SCRT aims to provide specialty mental health response and enhanced resources to adults in San Francisco who experience crises related to mental health and/or substance use disorders and are experiencing homelessness. Therefore, the study population will be defined based on age greater than 18 years, meeting criteria for homelessness in the 12 months prior to or 3 months following the crisis episode, and receipt of crisis care from any of San Francisco’s “front door” programs for people in an acute behavioral health crisis. These settings include two mobile crisis programs (Comprehensive Crisis Services and the SCRT), a crisis stabilization unit (DORE Urgent Care Clinic), and emergency psychiatric services (Zuckerberg San Francisco General Hospital’s Psychiatric Emergency Services [PES] and Emergency Department visits with a primary behavioral health diagnosis) (Fig 2). The population of housed adults utilizing acute behavioral health services will be utilized as a control group in the ITS sensitivity analyses.

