#### Index crisis episode

Conducting an ITS that includes a time-dependent outcome—in this case a routine care episode, acute care episode, housing assessment, or jail entry within 30 days following a crisis episode—requires defining an index crisis episode to start the clock for the outcome time interval. Furthermore, given that there may be multiple index episodes per unique individual, the index crisis episode needs to be defined per ITS interval, which, based on our preliminary power analysis, will be divided as one calendar month per interval. The index crisis episode will therefore be defined as the first instance in a given month that an individual has a crisis episode, with the 30-day post-crisis outcome period trailing the end date of the index episode.

We also need to account for the fact that a single crisis episode may result in multiple contacts with different settings in the acute behavioral health care system. To account for this variability, we will use our clinical knowledge of common care pathways as the basis for a crisis system map (Fig 2) that defines different sequences of care as either a step-up in service intensity (e.g., mobile crisis followed by crisis stabilization or ED), a step-down in service intensity (e.g., PES followed by crisis stabilization), or a distinct crisis episode that mostly likely signifies reutilization (e.g., PES followed by mobile crisis, or two consecutive mobile crisis episodes). We will then combine sequences with a step up or down in service intensity that occur within two or fewer days between the end of the first and start of the second clinical setting, so as not to miscount these care transitions as reutilization. This approach also allows us to create a variable describing these crisis system trajectories, thus allowing us to identify potential differences between index crisis episodes based on crisis system entry point and end point. All crisis services utilized three or more days after the index crisis episode end date will be considered separate from the index crisis episode.

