#### Covariates

Demographic variables for age at time of service, gender identity, sexual orientation, race/ethnicity, housing status and insurance status will be developed in accordance with existing SFDPH reporting guidelines. Gender identity will be determined by information on each person’s sex at birth as well as self-reported gender identity to create categories for cisgender male or female, transgender male or female, and genderqueer or nonbinary. Sexual orientation is based on self-report. Race and ethnicity are recorded separately in both EHR systems and will be cross-referenced and then combined into a single variable by replacing race with ethnicity for those who identify as Hispanic/Latinx [22]. SFDPH defines someone as a person experiencing homelessness if they utilize a service that indicates housing instability (e.g., emergency shelter) or self-report homelessness while accessing health care services. Insurance status at the time of an encounter will be based on EHR billing records and grouped into descriptive categories (e.g., private versus public insurance). A location variable using zip code will be based on last location documented prior to the crisis episode. Multiple imputation will be used to account for missing data.

Diagnoses associated with service encounters will be categorized using the primary ICD-10 diagnostic code based on the Health Care Utilization Project’s Clinical Classifications Software Refined (CCSR) [23]. Given the unreliability of diagnosis data at the time of a crisis encounter [24, 25], we will use diagnoses made in routine service settings in the 90 days prior to the index crisis episode and, only if routine care is unavailable, will use acute-care settings diagnoses.

Additional clinical variables will include whether the index crisis episode resulted in an involuntary psychiatric hold; suicidality as part of the presentation (based on ICD-10 Z codes as well as clinical documentation or indication for involuntary holds as “danger to self”); and violence risk (based on clinical documentation or indication for involuntary holds as “danger to others”) [26]. We will also control for continuous variables describing the number of crisis services, routine care, jail, or housing assessment encounters in the 12-months prior to the index crisis episode. We will also assess the number of crisis services, routine care, jail, or housing assessment encounters in the 12-months prior to the index crisis episode.

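### The ITS models adjust for involuntary hold at the index episode, and for variables partly defined from it, which SCRT itself can change, so the adjusted level and slope changes do not estimate the program's overall impact

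*Protocol article*

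**What the plan says.** The Interrupted time series analysis section specifies GEE models with time, period and interaction terms, and then states: "Models will be adjusted by the covariates described above". It names no model without those covariates.

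The Covariates section lists, among others:

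- "whether the index crisis episode resulted in an involuntary psychiatric hold";
- suicidality, which draws in part on the hold's danger-to-self indication ("based on ICD-10 Z codes as well as clinical documentation or indication for involuntary holds as"), and likewise the risk of violence, taken from clinical documentation or the corresponding danger-to-others indication;
- prior utilization, with a look-back counted from each index episode: "We will also control for continuous variables describing the number of crisis services, routine care, jail, or housing assessment encounters in the 12-months prior".

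On what SCRT does, the Program section says: "The team triages clients to the appropriate level of care, be it through resolution of the crisis in the field", with outpatient linkage or transport to acute care as the alternatives. The text after Fig 1 describes follow-up care "with the goal of linking clients to outpatient mental health and housing services, thus reducing reutilization of acute services". Under Study population, SCRT is itself one of the crisis entry points: "These settings include two mobile crisis programs (Comprehensive Crisis Services and the SCRT". The index episode is "the first instance in a given month that an individual has a crisis episode", so one person can contribute several. The Equity analysis section repeats each model within racial and ethnic strata.

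**The concern.** The aim set out in the Abstract and at the start of Methods is the impact of SCRT on four 30-day outcomes. A hold is worded as a result of the index episode. SCRT de-escalates and decides between resolution in the field and transport, so any effect it has on holds is part of its impact. Conditioning on the hold compares episodes with the same hold status before and after launch, which takes that part out of the estimate. If unmeasured severity drives both the hold and the outcome, conditioning also creates an association between period and severity within hold strata, and the coefficient is then not a clean direct effect either.

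Suicidality and violence risk share the problem to the extent that they are recorded through the hold: with fewer holds, the same presentation is less likely to be flagged by that route.

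The 12-month counts raise a related but weaker question. They cover the same services as the four outcomes, and their look-back moves into the SCRT period as the study goes on.

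**Working it through.** The plan gives no hold rate, effect size or sample size on this point, so there is no figure to reproduce. Three checks were made.

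**1. What the adjusted coefficient estimates.** Let S mark the period after launch and H the hold, with outcome risk = b + d·S + g·H. Averaging over the hold share (h0 before, h1 after) gives

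overall effect = d + g × (h1 − h0),

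while the model that includes H returns d. All inputs are assumptions: d = +3.0 percentage points and h0 = 50%. For example, with h1 = 30% and g = −10 points, 3.0 + (−10) × (0.30 − 0.50) = +5.0.

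| Hold share after launch | Overall, g = −10 | Overall, g = −20 | Overall, g = +10 | Hold-adjusted |
|---|---|---|---|---|
| 50% | +3.0 | +3.0 | +3.0 | +3.0 |
| 40% | +4.0 | +5.0 | +2.0 | +3.0 |
| 30% | +5.0 | +7.0 | +1.0 | +3.0 |
| 20% | +6.0 | +9.0 | 0.0 | +3.0 |

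Adjustment understates the overall effect when a hold lowers the outcome, overstates it when a hold raises it, and does no harm if SCRT leaves the hold share unchanged.

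**2. Adding unmeasured severity.** Each setting simulated 2,000,000 episodes with a baseline risk of 30%, d = +3 and g = −10 points. Without severity (hold share 50% to 30%), the overall effect was +4.9 and the adjusted effect +2.9. Severity was then allowed to raise the chance of a hold and to shift the outcome by 8 points per standard deviation (hold share 50% to 33%). The overall effect was +4.7 in both cases. The adjusted effect was +1.9 when severity lowers the outcome and +4.2 when it raises it. Neither adjusted value equals the direct effect of +3.0.

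**3. Calendar of the 12-month look-back.** From the period dates in the Interrupted time series analysis section, with launch in December 2020, count for each index month how many of the 12 preceding calendar months fall at or after launch.

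- Baseline (13 months): 0 of 12 throughout.
- Partial implementation (8 months): 0, 1, 2, 3, 4, 5, 6, 7 of 12; 28/96 = 29%.
- Full implementation (13 months): 8, 9, 10, 11, then 12 of 12 for December 2021 to August 2022; (8 + 9 + 10 + 11 + 9 × 12)/156 = 146/156 = 94%.

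The look-back is therefore wholly after launch for 9 of the 13 full-implementation months. Because SCRT is a counted crisis setting, its contacts can enter the crisis count only after launch.

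**The case against.** The article does not name a total-effect estimand, it computes crude monthly proportions for each outcome, and final covariate selection could sit in a fuller plan. Little of this stands for the hold. The stated aim is the program's impact, the level and slope changes come from the adjusted models, and the text says positively that those models are adjusted for the listed covariates. The comparisons with non-pilot areas and housed adults address secular change but do not undo adjustment for a consequence of the program.

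The objection is much stronger for the 12-month counts. Each count precedes its index episode, and for a 30-day outcome prior utilization is ordinary case-mix control. SCRT is a new entry point that takes calls formerly answered mostly by police, so it may bring into the cohort people who would not have been there before. Recent utilization is one of the few listed variables able to adjust for that. A reader might infer from the calendar that the counts are as unsuitable as the hold and must be dropped. The documents do not support that: dropping them trades one possible bias for another.

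A reader might also want to restrict the main model to variables fixed before SCRT. Insurance (taken at the encounter) and diagnosis (taken mainly from the preceding 90 days) would not meet that rule either, so it is not a workable line here.

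**Conclusion.** The point holds for the involuntary hold and for the parts of suicidality and violence risk that come from hold indications. Following the plan as written, the adjusted level and slope changes do not estimate the overall impact of SCRT, and the same applies within the equity strata.

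This rests on SCRT's stated role. The documents hold no data showing that SCRT changes hold rates, and if it does not, adjusting for the hold costs nothing in this respect.

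A reader might infer that an effective program is always pulled toward no effect, or that a definite share of the effect is lost. Neither follows. The sign depends on how a hold relates to each outcome and may differ across the four. The size depends on hold rates, hold effects and the share of episodes SCRT handles, none of which is given. The figures above are illustrations. They compare two periods and do not fit the segmented model, so they say nothing specific about the slope.

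For the counts, the calendar overlap is a fact and the SCRT contacts in the crisis count are a real change of meaning at launch. The net effect on bias is open, which calls for a sensitivity analysis and not for removal.

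**What to change.** In the main model for each of the four outcomes, and in each equity stratum, leave out the involuntary hold and any definition of suicidality or violence risk that uses the hold's indication. Versions based only on the other listed sources (Z codes for suicidality, clinical documentation for both) can be kept. Report the model that includes the hold variables as secondary, and state that it does not estimate the overall effect.

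Keep the rolling 12-month counts in the main model if wanted for case mix, and add a sensitivity analysis that refits without them, or with counts from a fixed window ending before November 2019. Such a window contains no SCRT contacts by construction. Where a rolling crisis count is kept in a sensitivity model, exclude SCRT contacts from it.

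The main-model change is a matter of covariate wording and needs no new data. The price is some loss of severity adjustment and of precision. A fixed early window is also a weaker measure of case mix: for August 2022 episodes it would end almost three years earlier, and it assumes records for that window can be drawn for everyone in the cohort.

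### The fixed pilot/non-pilot split does not fit a roll-out in several phases: areas launched between December 2020 and June 2021 are misclassified for part of the partial phase

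*Protocol article*

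**What the plan says.** The Interrupted time series analysis section lists several protections against threats to internal validity. The first is "the study design using two nonequivalent groups with staggered implementation", giving a "between-site comparison of the pilot catchment area relative to the non-pilot areas". Groups are assigned by zip code, from "crisis episodes with zip codes corresponding to neighborhoods that did or did not have the SCRT active during the partial implementation phase"; the sentence goes on to place this before coverage became citywide. Sub-analyses then examine "within-site differences for the pilot neighborhoods across the three time periods, and, separately, within-site differences for the non-pilot neighborhoods". The same two sets of neighborhoods are thus followed throughout, and the label does not change with time.

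The Program section says SCRT was first piloted in the highest-demand neighborhoods "in December 2020 and then was incrementally expanded to be citywide by June 2021". The Fig 1 caption describes the roll-out "by region, hours of operation, and launch date of each phase of expansion". The Interrupted time series analysis section treats December 2020 to July 2021 as a single partial-implementation period.

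**The concern.** A two-level label that stays constant over time cannot describe an intervention that reached areas in several steps. An area that launched between the first pilot and citywide coverage had no SCRT early in the partial phase and had it later. Whichever group it joins, its label is wrong for some months.

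This matters because the between-area contrast is the only listed protection that compares homeless adults with homeless adults at the same calendar date. The second protection uses non-homeless adults, and the third uses other outcomes. The Limitations section concedes that the effects of COVID cannot be fully accounted for, which makes a concurrent comparison more valuable. If the contrast is weakened by misclassification, a small or null difference between areas could be taken as evidence against an SCRT effect when it partly reflects the coding.

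**Working it through.** **Inputs from the article.** Partial phase: December 2020 to July 2021. First launch: December 2020. Citywide: by June 2021. The dates, areas and hours of the phases in between are in Fig 1, which is not shown here.

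**The plan's own count.** The article expects 8 to 12 monthly points per period. Counting calendar months from its dates gives 13 (baseline), 8 (partial) and 13 (full). The lower figure, 8, reproduces and is the one used here. The upper figure counts as 13, not 12; that is a separate slip with no bearing on this point.

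**Formula.** Assume an effect of the same size in all areas and equal episode volume in every month. Then

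share of effect kept = (mean exposed share of months, pilot group) − (mean exposed share of months, non-pilot group).

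**Reading A: pilot means the first catchment only.** The pilot group is exposed in all 8 months (mean 1).

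- Non-pilot areas exposed only from July 2021: 1/8 = 0.125, so 1 − 0.125 = 0.875 is kept.
- Non-pilot areas exposed only from June 2021: 2/8 = 0.25, so 1 − 0.25 = 0.75 is kept.
- Non-pilot coverage growing evenly to full in July (assumption): (0 + 1/7 + 2/7 + … + 7/7)/8 = 4/8 = 0.50, so 0.50 is kept.
- Non-pilot coverage growing evenly to full in June (assumption): (0 + 1/6 + 2/6 + 3/6 + 4/6 + 5/6 + 1 + 1)/8 = 4.5/8 = 0.5625, so 0.4375 is kept.
- The same even growth, with the contrast stopped at the end of May: 2.5/6 = 0.417, so 0.583 is kept.

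**Reading B: pilot means any area active before citywide coverage.** The non-pilot group is then unexposed through May, but late joiners bring unexposed months into the pilot group. Suppose half the pilot areas launched in December and half in March (assumption).

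- December to May: pilot exposure is (3 × 0.5 + 3 × 1)/6 = 0.75 and non-pilot exposure is 0, so 0.75 is kept.
- All 8 months, with non-pilot areas exposed from June: pilot (3 × 0.5 + 5 × 1)/8 = 0.8125, non-pilot 0.25, so 0.5625 is kept.

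**What this could cost in power.** The article states no power or effect size. Take, as an assumption, a contrast with 80% power at two-sided 5% when exposure is coded correctly. With a share f kept, power = Φ(f × (1.960 + 0.842) − 1.960):

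| f | power |
|---|---|
| 0.875 | 69% |
| 0.75 | 56% |
| 0.50 | 29% |
| 0.4375 | 23% |

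**The case against.** The strongest reply is that the definition is tied to the time before citywide expansion. An area launched in a second or third step did have SCRT active in that time, so it would belong to the pilot group, and the non-pilot group would stay clean until citywide launch. This stands as a possible reading. A reader might infer that the comparison group was steadily being treated from December on; the text does not establish that, and the 0.44 to 0.50 figures hold only under Reading A with even growth. The reply does not remove the problem, because late joiners then dilute the pilot group. Nor does the article say which reading applies, since the phrase pilot catchment area suggests the narrower one.

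Other stronger inferences are also unsupported:

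- **A flat bias towards no effect.** This needs similar effects across areas. The article itself calls the groups nonequivalent and says the highest-demand neighborhoods went first.
- **Change in non-pilot areas mistaken for secular trend.** The partial phase has its own period and slope terms, and the underlying trend is anchored in the 13 baseline months.
- **A decision to ignore launch dates.** The article calls the roll-out staggered and cites Fig 1. It does not say the dates will go unused, but the contrast it specifies does not use them.
- **Limited operating hours as an error.** Hours are mentioned only in the Fig 1 caption, and they can be regarded as part of the programme as delivered.

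A further reply is that zip code is the last location documented before the episode, and that the Limitations section would drop the partial segment if location data are too incomplete. That answers missing location, not exposure that changes over time.

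**Conclusion.** The point holds as a design weakness in one supporting analysis. A fixed pilot/non-pilot label does not match the roll-out the article describes, and areas launched between December 2020 and June 2021 are misclassified for part of the partial phase on either reading. The contrast is attenuated if effects are similar across areas.

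The amount is unknown without the Fig 1 dates. Over the 8 months, with the pilot group exposed throughout, it runs from 0.75–0.875 of the effect kept (non-pilot areas exposed only at citywide launch) down to about 0.44–0.50 (even growth from December, assumed).

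A reader might infer that the study's main result is compromised. It is not: the citywide three-period series, the comparison with non-homeless adults and the non-equivalent outcomes do not use this split, and a within-area comparison of baseline with full implementation is untouched.

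**What to change.** Replace the fixed label with a time-varying exposure:

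- Code each index episode as SCRT-active or not from the launch date of its zip code's area, as shown in Fig 1.
- Fit area and calendar-month terms, with not-yet-launched areas as the comparison (a staggered difference-in-differences).
- End the between-area contrast when no unlaunched area remains, which by the Program section is at citywide coverage in June 2021.
- Coding by operating hours, where the episode time is recorded, is at most an optional sensitivity analysis.

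The cost is a change of analysis wording and one derived variable, built from the zip code already planned and a schedule the authors already publish. There are two drawbacks. Intervals will be wider in the later months, when few unlaunched areas remain. The contrast will also still rest on the last documented zip code, whose completeness the article already doubts.
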